### Safety protocol

The safety protocol is comprised of three levels of security including: (1) system and privacy protection; (2) online safety and (3) clinical safety.

The *Rebound* platform is hosted on an Amazon Web Services web server. Amazon Web Services and Orygen Digital meet standards of responsible business practice. Identity management and networking are handled by Orygen Digital’s Engineering Department according to Orygen (National) Standards, which meet Australian research requirements. In addition, MOST has a wide range of measures to secure the application and database against unauthorised access. These measures conform to industry best practice as defined by the Open Web Application Security Project (www.OWASP.org). Privacy and online safety are managed in accordance with the Australian Communications and Media Authority.

At onboarding, the *Rebound* clinician carries out an initial orientation with *Rebound* participants, including details of the terms of use. Participants are required to accept and comply with the guidelines for safe use of *Rebound*. When needed, participants are offered guidance on appropriate usage of the system. All users are asked to nominate an emergency contact person, such as a close family member. *Rebound* includes a ‘report function’ that enables young people to report a concern about any material posted by a user. The moderator assesses the report and responds accordingly, which may include removing material and, in some cases, deactivating or restricting the poster person’s account. Participants are also able to hide their profile and activity should they become concerned about their privacy.

Clinical risk is managed through both manual and automated procedures. First, clinical moderators monitor the system two times per day on weekdays and one time per day on weekends for evidence of clinical risk or deterioration. Any detected increased risk activates the *Rebound* risk and safety protocol, which includes one or more of the following: a risk assessment with the young person, informing the research team, alerting the emergency contact nominated by the participant and liaising with suitable emergency services where necessary. In addition, the system incorporates visible emergency guidelines and contact information. Finally, *Rebound* includes an automated keyword detection function, which activates each time a participant posts a contribution indicative of clinical risk or that contains potentially offensive words. The function blocks posts with notifications sent to the young person and the moderator, who can ‘unblock’ the post should they determine it unproblematic.

In the event of a clinically significant deterioration of symptoms, increased risk of suicide or a hospital admission, a clinical moderator performs an assessment to determine the risks and benefits of a temporary withdrawal from *Rebound*. Based on this assessment, and in consultation with the young person, the clinical moderation team determines whether their account is temporarily suspended, or their level of access is restricted. Following suspensions or restrictions to a user’s account, the clinician will contact the young person at monthly intervals to ascertain whether the account is to be reactivated.

### Outcome measures

Multiple methods will be employed to assess study outcomes (see table 3). These include independent observer ratings, self-report and usage data from the *Rebound* system.

**Table 3 T3:** Schedule of outcomes and measures

	Screening/baseline	3 months	6 months	9 months	12 months	15 months	18 months	
**Primary outcome and measure**								
Relapse of MDD (SCID-5-RV: depression module)	x	x	x	x	x	x	x	
**Secondary outcomes and measures**								
Depressive symptoms (QIDS-SR)	Monthly							
Time to relapse (SCID-5-RV: depression module)	x	x	x	x	x	x	x	
Time to remission (SCID-5-RV: depression module)	x	x	x	x	x	x	x	
Rate of remission (SCID-5-RV: depression module)	x	x	x	x	x	x	x	
Time in remission (SCID-5-RV: depression module)	x	x	x	x	x	x	x	
Anxiety (GAD-7)	x		x		x		x	
Vocational status (RUQ)	x		x		x		x	
Cost-effectiveness (RUQ)	x		x		x		x	
**Therapeutic mechanisms and measures**								
Mindfulness skills (FMI)	x		x		x		x	
Self-compassion (SCS-SF)	x		x		x		x	
Social support (SPS)	x		x		x		x	
Rumination (RRS-SF)	x		x		x		x	
**Exploratory outcomes and measures**								
Stress (PSS)	x		x		x		x	
Social anxiety (LSAS)	x		x		x		x	
Loneliness (UCLA Loneliness Scale)	x		x		x		x	
Self-efficacy (Self-Efficacy Scale)	x		x		x		x	
Self-esteem (Rosenberg SES)	x		x		x		x	
Social and general functioning (SOFAS)	x		x		x		x	
Suicidal ideation and attempts in past 6 months (CSSRS)	x		x		x		x	
Deliberate self-harm (Risk Taking and Self-Harm Inventory†)	x		x		x		x	
Psychological well-being (BPNSS)	x		x		x		x	
Quality of life (AQoL-8D)	x		x		x		x	
Behavioural activation (BADS-SF)	x		x		x		x	
Sleep quality (PSQI)	x		x		x		x	
Strengths use (SUS)	x		x		x		x	
Medication adherence (RUQ)*	x		x		x		x	
Substance use (ASSIST)*	x		x		x		x	
Digital phenotype (AWARE-Light)	Continuous							
Affective and cognitive reactivity and social support (SEMA3 application)	Daily							
**Intervention group-only outcomes and measures**								
Intervention acceptability (qualitative evaluation via semistructured interview)							x	
Therapeutic alliance (WAI-C, WAI-T)	x		x		x		x	
Intervention use (ie, frequency, duration, pattern)	Continuous							

* Potential covariates.

† Risk Taking and Self-Harm Inventory for Adolescents.

AQoL-8DAssessment of Quality of Life - 8 DimensionsASSISTAlcohol, Smoking and Substance Involvement Screening Test BADS-SFBehavioural Activation for Depression Scale-short formBPNSSBasic Psychological Needs Satisfaction ScaleCSSRSColumbia-Suicide Severity Rating ScaleFMIFreiburg Mindfulness InventoryGAD-7Generalized Anxiety Disorder 7-item scaleLSASLiebowitz Social Anxiety ScaleMDDmajor depressive disorderPSQIPittsburgh Sleep Quality IndexPSSPerceived Stress ScaleQIDS-SRQuick Inventory of Depressive Symptomatology-Self-ReportRRS-SFRuminative Responses Scale - short formRUQResource Use QuestionnaireSCID-5-RVStructured Clinical Interview for DSM-5 Disorders, Research VersionSCS-SFSelf-Compassion Scale Short FormSEMA3Smartphone Ecological Momentary AssessmentSESSelf-Esteem ScaleSOFASSocial and Occupational Functioning Assessment ScaleSPSSocial Provisions ScaleSUSStrengths Use ScaleUCLAUCLA Loneliness Scale (Version 3)WAI-CWorking Alliance Inventory client versionWAI-TWorking Alliance Inventory therapist version

#### Primary outcome and measure

The primary outcome is *relapse rate* (accumulated over 18 months) of MDD. Relapse will be defined as a return, for at least 2 weeks, of symptoms sufficient to meet DSM-5 criteria for MDD (as determined by the SCID-5-RV)^34^ at any time in the 18 months post randomisation. This definition of relapse is the one most commonly used in clinical studies.^39^ Measurement of relapse will be carried out every 3 months (ie, at 3, 6, 9, 12, 15 and 18 months). Telephone administration of the SCID is a valid method for measuring MDD.^40^ Data from the Quick Inventory of Depressive Symptomatology Self-Report^41^ may also be used to supplement the SCID assessment. A number of strategies will be embedded to promote participant retention, including a generous assessment window, flexible availability of RAs, minimal data collection at most timepoints and honing RA interview skills to minimise time commitment at larger assessment points.

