### Participants

Inclusion criteria for participants are: (a) age 14 to 27 years inclusive; (b) able to read and converse in English; (c) able to provide informed consent; (d) able and willing to nominate an emergency contact person, such as a close family member; (e) diagnosis of MDD (current, partial or full remission) corresponding to the current episode of care as measured by the SCID-5-RV;^34^ and (f) ≥ 1 episode of MDD if in partial remission at time of screening assessment or ≥2 episodes of MDD (including the current episode) if current MDD or MDD in full remission at time of screening assessment.

Exclusion criteria are: (a) inability to converse in or read English; (b) acute risk of self-harm requiring urgent intervention (ie, suicidal ideation with a current plan and intent to enact this plan) at time of screening assessment; (c) a diagnosed permanent developmental delay or intellectual disability; (d) current or past episode of mania or hypomania; and (e) previous exposure to a MOST platform.

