### Enrolment and randomisation

Participants are recruited from primary and specialist youth mental health services. In Victoria, study research assistants (RAs) attend weekly clinical review meetings at YMC and headspace services to identify eligible clients. In NSW, a study clinical liaison has been appointed at satellite sites to actively facilitate recruitment at the site. The study liaison attends clinical review meetings, engages with treating clinicians and screens clinical files to identify potentially eligible clients. The study liaison introduces the trial to the client and obtains consent to share contact details with Orygen. Young people can also self-refer via the study recruitment page on the Orygen website.

The RA contacts potential participants, provides a detailed explanation about the trial and offers to answer questions. All participants are required to provide informed, signed consent. Parental or legal guardian consent is required for participants under 18 years of age. Once consent is obtained, the participant is enrolled in the trial and a screening assessment to assess eligibility is conducted by the RA. Once eligibility is established, the baseline assessment is completed. After completing the baseline assessment, the participant is randomised by the RA via a secure online Research Project Management System (RPMS). The RPMS sends an automated email to the study coordinator and principal investigator, notifying them of the outcome of randomisation. The study coordinator informs the participant of the allocation. Participants are reimbursed for their time for each assessment completed.

The randomisation schedule is generated by a statistician independent of the study, programmed in the RPMS and not accessible by the study team. Participants are randomly assigned to the treatment condition via the RPMS using randomly permutated blocks with a 1:1 allocation ratio. Participants are stratified by current MDD status (current, partial or full remission), number of previous MDD episodes (≤ 2 or ≥ 3), age (<18 years and ≥18 years), sex at birth and by treatment centre.

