### Data analysis and management

#### Sample size

Sample size was determined by power analysis using G*Power 3. The primary outcome is difference in accumulated relapse rate over 18 months. A previous relapse prevention study in youth MDD reported a relapse rate at an 18-month follow-up of 62% for TAU and 36% in the relapse prevention group (OR=2.9).^48^ Since *Rebound* will be compared against an enhanced TAU, we assume a smaller effect (OR=2.5), for which a total sample of 192 people is required to achieve 85% power (alpha=0.05). A total of 255 participants will be recruited, allowing for a 25% attrition rate. This compares favourably with the attrition rates in the *Rebound* pilot (7%) and is comparable at an 18-month follow-up to the Horyzons RCT (25%).^14 15^

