#### Analysis of outcomes

Primary analyses will be undertaken on an intention-to-treat basis. Group differences in accumulated relapse rate at 18 months (primary outcome) will be tested using Fisher’s exact test. The Cox proportional hazards regression model (survival analysis) will be used to model time to relapse and rate of remission in each group, which will also be used to derive the hazard function reflecting the instantaneous probability of relapse/remission at any time over the 18-month follow-up.^49^ Finally, group differences (*Rebound* plus TAU vs enhanced TAU) in change over time in the continuous secondary outcomes across the 18-month follow-up will be examined using random-effects models. Random-effects models allow for estimation of between-person differences (ie, group effects) in within-person slopes (ie, change trajectories in secondary outcomes) and are the preferred methods for analysing clinical trial data.^50^

Mechanism of action analyses will be conducted using a multilevel structural equation modelling framework to assess mediation.^51^ Specifically, person-specific slopes representing change over time in the proposed mechanism-of-action variables will be examined as mediators of the effect of treatment group (*Rebound* vs control) on risk of relapse.

Additional analyses will use multiple imputation to assess the robustness of the findings to the choice of method for handling missing data. Additional comparisons between treatment groups based on completers-only analyses will be conducted. Analyses will be undertaken in accordance with The International Council for Harmnonisation (ICH) 9 guidelines including a full analysis as well as per protocol set. The per protocol sample will be defined based on receiving a prespecified minimal exposure to the online intervention (ie, more than 16 logins over the 18-month intervention period).

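### The primary relapse outcome, as worded, places current-episode entrants who never remit with those who stay well, and the 85% power assumes everyone is at risk of relapse from randomisation

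*Protocol article*

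**What the plan says.** Eligibility (Participants) requires a "diagnosis of MDD (current, partial or full remission) corresponding to the current episode of care". Entry during an episode is explicit: the episode-count criterion asks for "≥2 episodes of MDD (including the current episode) if current MDD or MDD in full remission at time of screening assessment". Enrolment and randomisation makes this status a stratification factor, with current MDD as one level.

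Primary outcome and measure gives the event: "Relapse will be defined as a return, for at least 2 weeks, of symptoms sufficient to meet DSM-5 criteria for MDD", occurring "at any time in the 18 months post randomisation". It gives no rule for a participant whose baseline episode does not end.

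Analysis of outcomes compares accumulated relapse at 18 months by Fisher's exact test on an intention-to-treat basis. Remission rate, time to remission and time in remission are secondary outcomes only.

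Sample size takes its rates from an earlier youth relapse-prevention study, which "reported a relapse rate at an 18-month follow-up of 62% for TAU and 36% in the relapse prevention group". It then assumes an odds ratio of 2.5 and arrives at 192 participants for 85% power, and 255 after 25% attrition.

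**The concern.** A participant in a current episode at randomisation must remit before symptoms can return. The endpoint is binary and analysed by intention to treat, so each such person needs a yes or a no. Three readings are available, and each distorts the result:

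- **Literal wording.** A never-remitter has had no return of symptoms and falls in the no-relapse cell with participants who stayed well.
- **Any full-criteria MDD after randomisation is an event.** Persistent entrants become relapses by the first assessment. This sits badly with the idea of a return and counts baseline illness as an outcome.
- **Never-remitters are left out.** This departs from intention to treat and selects participants on a post-randomisation event that treatment may alter.

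Treatment is meant to alter remission. The secondary hypotheses in the Introduction include time to remission, and the Human support section describes content tailored to users who are actively depressed. At stake are what the headline relapse comparison estimates and how much power it has.

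**Working it through.** **Inputs from the protocol article:** control relapse 62%; odds ratio 2.5; alpha 0.05; 1:1 allocation; 192 completers, so 96 per arm. **Not given, so assumed:** the share *f* entering in a current episode, and the probability *r* that such an entrant remits within 18 months.

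**Step 1: reproduce the plan.** Control odds are 0.62/0.38 = 1.632. Dividing by 2.5 gives 0.653, so the Rebound rate is 0.653/1.653 = 39.5%. The two-sided two-proportion formula

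n = [1.960·√(2p̄(1−p̄)) + 1.036·√(pC(1−pC) + pT(1−pT))]² / d²

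with p̄ = 0.507 and d = 0.225 gives 87.0 per arm. The continuity correction (n/4)·[1 + √(1 + 4/(n·d))]² gives 95.7, hence 96 per arm and 192 in total. Exact two-sided Fisher power at 96 per arm is 85.4%. For attrition, 255 × 0.75 = 191.25, which agrees with 192 up to rounding. The stated figures therefore hold if 62% and 39.5% apply to every participant.

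**Step 2: relapse rate as worded.** Let *q* be the relapse probability among those who are ever at risk. Then

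arm rate = q·(1 − f + f·r).

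This increases with *r* at slope f·q, so more remission means more counted relapse. The formula gives late remitters the same *q* as those at risk from day one.

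Example with f = 20% and remission of 50% (control) vs 70% (Rebound):
- control: 0.62 × (0.80 + 0.20 × 0.50) = 0.62 × 0.90 = 55.8%
- Rebound: 0.395 × (0.80 + 0.20 × 0.70) = 0.395 × 0.94 = 37.1%
- odds ratio 2.14, power about 70%

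Exact two-sided Fisher power, 96 per arm, q = 62% vs 39.5%:

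| Remission, control vs Rebound | f = 20% | f = 40% | f = 60% |
|---|---|---|---|
| 80% vs 90% | 79% | 72% | 63% |
| 50% vs 50% | 77% | 67% | 57% |
| 50% vs 70% | 70% | 49% | 29% |

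The second row shows that power falls even when treatment has no effect on remission.

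**Step 3: no effect on relapse, better remission under Rebound.** Take q = 62% in both arms, with remission 70% on Rebound and 50% on control.
- f = 20%: Rebound 0.62 × 0.94 = 58.3%, control 0.62 × 0.90 = 55.8%
- f = 50%: Rebound 0.62 × 0.85 = 52.7%, control 0.62 × 0.75 = 46.5%

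Rebound shows somewhat more relapse only because more of its participants recovered. The chance of a significant result against Rebound is 3.9% and 10.8%, compared with 1.7–1.8% when the arms are identical.

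**Step 4: count never-remitters as unfavourable.** This adds f·(1 − r) to each arm. With 50% vs 70% remission, the rates at f = 20% are 55.8 + 10.0 = 65.8% vs 37.1 + 6.0 = 43.1% (power 86%). At f = 60% they are 73.4% vs 50.4% (power 89%). With equal 50% remission the power is only 77% and 58% at those values of f. This scoring removes the penalty on remission, but it does not restore power when remission is equal.

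**The case against.** No sentence in the article says that never-remitters are scored as no relapse. That follows from the word for a return combined with a binary intention-to-treat test. A separate analysis plan exists and may contain a scoring rule. This is fair as to certainty. It does not clear the definition, because choosing among the readings changes what the primary outcome measures.

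Several mitigating features are real. The remission outcomes and monthly depressive symptoms are prespecified, so persistent depression would be visible elsewhere. Stratified randomisation balances baseline status between arms. Neither changes the primary definition.

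A reader might infer four stronger things that the article does not support:

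- **That the trial could show harm while Rebound truly improves both remission and relapse.** At the planned relapse effect the expected direction reverses only if 0.62·(1 − f + f·rC) < 0.395·(1 − f + f·rT). Even with every Rebound entrant and no control entrant remitting, this needs f above 1 − 0.395/0.62 = 36%. At f = 50% it needs control remission below 27% with 100% on Rebound. Those inputs are extreme. The reversal in Step 3 assumes no relapse benefit.
- **That the 62% and 36% rates cannot apply to current-episode entrants.** The source study's entry criteria are not shown. The article gives no basis for applying the rates to this stratum, which is a weaker statement.
- **That the power loss is known and large.** Assumed rates can be picked so that the effect in the current-MDD stratum cancels exactly: 50% remitting and half relapsing, against 75% remitting and a third relapsing, is 25% in both arms. Power then runs from 66% at f = 20% to 21% at f = 60%. Nothing in the article supports those particular rates.
- **That the Cox analyses share the fault.** The article says only that "The Cox proportional hazards regression model (survival analysis) will be used to model time to relapse and rate of remission in each group". It does not fix who is in each risk set, which is ordinary analysis-plan detail.

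**Conclusion.** The point holds as a defect in the primary definition. Current-episode entrants are a planned stratum, the event presupposes recovery, and no passage says how someone who never recovers is scored. Under the literal wording, persistent depression counts the same as staying well, and the comparison mixes relapse prevention with remission.

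The stated 85% power is arithmetically correct, but it is conditional on all 192 completers being at risk from randomisation. The size of any loss cannot be derived from the article. Over 20–60% current-episode entry, the three assumed remission patterns give power from 79% down to 29%, the lowest value needing both a high current-MDD share and a 20-point remission difference. The penalty on better remission needs a difference in remission between arms; the misclassification and the dilution do not. The definition should be settled before results are known by arm.

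**What to change.** Before outcome data are seen by arm, put the following in the protocol and analysis plan:

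1. State how a participant in a current episode at randomisation who never remits is scored on the primary outcome.
2. Stratify the primary analysis by baseline MDD status.
3. Report relapse among participants in partial or full remission at randomisation as the key supportive estimate. Baseline status is a stratification factor, so this comparison does not depend on post-randomisation recovery.
4. Add a sensitivity analysis in which relapse, or never remitting by 18 months, is the unfavourable outcome. Keep the printed definition visible beside it.
5. Restate that 85% power assumes all 192 completers are at risk of relapse, and give the range over the actual baseline mix.

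Replacing the primary outcome with the composite is not needed. It would depart from the stated relapse hypothesis at a late stage: the Discussion says recruitment ended in September 2023 and follow-up was to conclude in March 2025. Timing matters because the trial masks raters only; the coordinator and principal investigator are notified of each allocation. The rule should therefore be fixed and dated without sight of outcomes by arm.

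No new data are needed, since baseline status and three-monthly SCID assessments are already scheduled. The cost is dated wording, a little more analysis and a less favourable power statement.

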#### Secondary outcomes and measures

Secondary outcomes and measures include:

*Depressive* symptoms will be measured by the QIDS self-report instrument^41^ monthly for 18 months.*Time to relapse* will be derived from the SCID-5-RV (Module A: Mood Episodes) at 3, 6, 9 12, 15 and 18 months.*Time to remission* will be derived from the SCID-5-RV (Module A – Mood Episodes) at 3, 6, 9, 12, 15 and 18 months.*Rate of remission* will be derived from the SCID-5-RV (Module A – Mood Episodes) at 3, 6, 9, 12, 15 and 18 months.*Time in remission* will be derived from the SCID-5-RV (Module A: Mood Episodes) at 3, 6, 9, 12, 15 and 18 months.*Anxiety* will be measured by the Generalized Anxiety Disorder 7-item scale^42^ at baseline, 6, 12 and 18 months.*Vocational status* will be self-reported by participants at baseline, 6, 12 and 18 months (including the participant’s report of employment and educational activities in between assessments).*Cost-effectiveness* will be assessed using a self-reported Resource Use Questionnaire (RUQ) to determine the broader resource use of participants (eg, community mental health services, hospitalisations, work and educational impacts) and the Assessment of Quality of Life - 8 Dimensions (AQoL-8D) questionnaire, which measures health-related quality of life and can be used to calculate quality-adjusted life years (QALYs).^43^

